## **1.2 - EXPECTED RESULTS AND PROSPECTS**

The study will be conducted in patients between the ages of 50 and 85 years with knee osteoarthritis for which total knee arthroplasty has been scheduled by the surgeon. Two patient groups will be studied: one of the two groups will undergo four group sessions including therapeutic education and physical exercises, a knee arthroplasty guide and an exercise CD at least 2 months before the intervention; the other group (control group) will receive the usual information and advice given by the surgeon and according to each centre, and a knee arthroplasty guide.

If this programme is confirmed to be effective, it should lead to a reduction in the length of hospital stay and rate of transfers to rehabilitation care facilities, achieving quicker and more complete functional recovery, improving the patient's quality of life and satisfaction, and reducing treatment costs.

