### **II.2 - SECONDARY OBJECTIVES**

The secondary objectives in these patients with knee osteoarthritis for whom a TKA is scheduled are as follows:

1) Clinical assessment at 6 months and 12 months:

- a. function (WOMAC);
- b. pain (numeric scale 0-100);
- c. quality of life (SF-12 and EQ-5D-3L);
- d. number of steps (pedometer);
- e. treatment satisfaction.

2) Health economics evaluation for the intervention. The costs of the two strategies will be compared at 6 and 12 months by taking into account the perspectives of the payer (Health Insurance) and the healthcare system. In addition, patients' quality of life will be estimated at the enrolment visit, and 6 months and 12 months after the procedure, using the EuroQoL questionnaire (EQ-5D-3L) [Brooks 1996, Fransen 1999] (Annex 5). In the event that the most expensive strategy is the one that provides the best medical outcome and the best quality of life, we will carry out a cost-effectiveness analysis.

Implementing and evaluating complex intervention strategies such as combining educational and supervised exercise programmes is complicated and raises a number of specific methodological issues. Recently published recommendations [Craig 2008] highlight the need to take into account multiple endpoints. Indeed, complex interventions have multiple objectives (improving function, patient information and changing patient behaviour in terms of physical activity and weight-loss).

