## **IX.2 - JUSTIFICATION OF THE REQUIRED NUMBER OF SUBJECTS**

The first primary endpoint is the percentage of patients able to be discharged from the surgical department on D4, plus or minus 1 day. The expected percentage in the control arm is 20%. The sample size of 130 patients per arm will allow for an odds ratio of 2.15 (logrank test) with a power of 90% for a p-value of 2.5% in bilateral formulation in order to take into account the double endpoint. The second primary endpoint is the WOMAC function area under the curve analysis at 6 months. The total number of 260 subjects enrolled (130 per group) will allow to demonstrate an effect size of 0.45 for comparison of the average areas under the curve with a power equal to 90% (p-value equal to 2.5%, Mann-Whitney test). Taking into account approximately 10% losses-to-follow-up before the procedure, the number of patients to be enrolled into each study arm will be approximately 150, giving a total of 300.

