### **Health economics evaluation.**

The intervention costs (from the Health Insurance perspective for the basic calculation) will be compared. In the event that the most expensive strategy is the one which provides the best functional outcome and quality of life, we will carry out a cost-effectiveness analysis. The values will be taken from the EuroQol questionnaire. The base ratio estimation will be completed with a sensitivity analysis (particularly on the pricing of education procedures) and a bootstrap estimation of confidence intervals.

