| Patient follow-up         | Between 14 and 15 months, depending on the time between the enrolment visit and the intervention for the educational programme associated with an exercise programme                                                                                                                                                                                                                                                                                                                                                                                                                                                                                                                                                                                                                                                                                                                                                                                                                                                                                                 |
| Study aim                 | 
Primary objective:
To assess the effectiveness of a standardised education and exercise programme proposed before a total knee arthroplasty for knee osteoarthritis, in terms of:
 
 
- ability, at discharge from the surgical department measured at D4, plus or minus 1 day, to carry out lying-sitting and sitting-standing transfers, walk 30 metres and go up and down one flight of stairs;
 
- speed of functional recovery within the first 6 months (area under the curve of the function subscale of the WOMAC index).
 
 
Secondary objectives:
 
 
- To assess the effectiveness of the intervention in terms of pain, function (personalised WOMAC index), quality of life, number of steps and treatment satisfaction at months 6 and 12;
 
- To estimate and compare the cost of the strategies and, where appropriate, carry out a cost-utility analysis.
 
                                                     |

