## **8 Health economics analysis**

The EQ-5D scores will be converted into utilities based on French value tables. The utilities imputed for the periods corresponding to the interval between 2 collections will be multiplied by the corresponding durations to obtain QALYs. The differences in QALYs will be compared between the two groups.

The intervention will be valued on a flat-rate basis based on the time spent by the professionals as described in the protocol and by multiplying the estimated cost of each session by the proportion of patients having undergone the sessions.

Hospital admissions related to the pathology (imputed during the end-of-study meeting) will be valued based on 1) ENCC (French national hospital costs study database) costs and 2) rates. The costs will be estimated for each patient and the average costs in each arm will be compared using non-parametric tests.

The incremental cost-utility ratio will be calculated by comparing the difference in average costs with the difference in average QALYs, with a bootstrap sensitivity analysis.

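### SAP section 8 omits the protocol's condition on the cost-utility ratio, and neither document says how to summarise bootstrap replicates when the QALY difference is near zero

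*Supplement*

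**What the plan says.** SAP section 8 (Health economics analysis) converts EQ-5D scores to utilities and then to QALYs, compares QALYs between groups, estimates a cost for each patient and compares average costs. It ends: "The incremental cost-utility ratio will be calculated by comparing the difference in average costs with the difference in average QALYs", "with a bootstrap sensitivity analysis". No condition on the signs of the two differences is attached, and nothing is said about dominance or about a QALY difference near zero.

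The protocol attaches a condition twice. Section IX.4, item 4, introduces the ratio analysis with "In the event that the most expensive strategy is the one which provides the best functional outcome and quality of life". Section II.2 does the same with "In the event that the most expensive strategy is the one that provides the best medical outcome and the best quality of life". After its condition, IX.4 asks that the base ratio be accompanied by a sensitivity analysis and "a bootstrap estimation of confidence intervals".

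The SAP's own summary is softer than its section 8: "To estimate and compare the cost of the strategies and, where appropriate, carry out a cost-utility analysis". It does not define when the analysis is appropriate. The endpoint lists in the SAP summary and in protocol VI.2 name the ratio without a condition.

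On the hoped-for result, protocol I.2 says that an effective programme should improve "quality of life and satisfaction, and reducing treatment costs".

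**The concern.** There are two gaps, one inside the other.

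The first is that the operational text does not carry the protocol's condition. If the hoped-for result occurs (cheaper and better), an analyst who follows section 8 to the letter computes a negative ratio. Its sign does not separate a dominant strategy from a dominated one, and its size does not rank results.

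The second would remain if the condition were restored. The condition depends on the observed point estimates, whereas bootstrap replicates scatter around them. When the QALY difference is small against its standard error, some replicates have a negative denominator and others a denominator close to zero. The sorted ratios then mix four economic conclusions on one number line, and their 2.5th and 97.5th percentiles are not limits of anything a decision-maker can use. The protocol asks for exactly such an interval, the SAP asks only for an unspecified bootstrap, and neither says how to handle the mixture.

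At stake is a usable statement of uncertainty for the health-economic objective.

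**Working it through.** **No figure to reproduce.** The documents give no QALY SD, cost SD or expected difference for the economic analysis. The SDs and effects below are assumptions, shown as ranges. From the protocol come 150 randomised per arm and, after losses, 130 per arm (IX.2: "The total number of 260 subjects enrolled (130 per group").

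**Sign and size of the ratio.** Ratio = ΔC/ΔQ, intervention minus control.

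- Cheaper and better: −500 euros / +0.02 QALY = −25,000.
- Dearer and worse: +500 euros / −0.02 QALY = −25,000.
- Cheaper and better, with ΔC fixed at −500: a gain of 0.005, 0.02 or 0.05 QALY gives −100,000, −25,000 or −10,000. The larger the gain, the closer the ratio is to zero.

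**Share of replicates with a negative denominator.** SE(ΔQ) = SD × √(2/n), and the share is Φ(−d/SE) for a true difference d, treating replicates as normal and centred on d.

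| n per arm | QALY SD | SE | d = 0 | d = 0.01 | d = 0.02 | d = 0.05 |
|---|---|---|---|---|---|---|
| 150 | 0.15 | 0.0173 | 50% | 28% | 12% | 0.2% |
| 150 | 0.20 | 0.0231 | 50% | 33% | 19% | 1.5% |
| 150 | 0.25 | 0.0289 | 50% | 37% | 24% | 4.2% |
| 130 | 0.15 | 0.0186 | 50% | 30% | 14% | 0.4% |
| 130 | 0.20 | 0.0248 | 50% | 34% | 21% | 2.2% |
| 130 | 0.25 | 0.0310 | 50% | 37% | 26% | 5.3% |

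Worked example: 0.20 × √(2/150) = 0.0231; 0.02/0.0231 = 0.866; Φ(−0.866) = 0.19.

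**What this does to a percentile interval.** ΔC and ΔQ were simulated as independent normals with 130 per arm and a cost SD of 3,000 euros, so SE(ΔC) = 3,000 × √(2/130) = 372. Limits are in euros per QALY and are approximate, because the tails of a ratio are unstable between runs.

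| True ΔC, ΔQ | QALY SD | 2.5 to 97.5 percentile range |
|---|---|---|
| −500, +0.02 (cheaper, better) | 0.2 | −260,000 to +240,000 |
| +500, +0.02 (dearer, better) | 0.2 | −230,000 to +250,000 |
| +1,000, +0.05 (dearer, better) | 0.2 | about 0 to +120,000 |
| +1,000, +0.05 (dearer, better) | 0.1 | +5,000 to +47,000 |

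In the first row about 72% of replicates are cheaper and better, 19% cheaper and worse, 7% dearer and better, and 2% dearer and worse. That breakdown is informative, but the interval hides it. The second row lies inside the protocol's condition and its interval is no more usable. The last two rows show the difficulty shrinking as the effect becomes clear relative to its standard error.

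**Net monetary benefit for comparison.** For a willingness to pay of λ per QALY, NMB = λ × ΔQ − ΔC. It has no denominator, is linear in both differences, and is positive exactly when the intervention is worth its cost at λ. The same replicates give an ordinary bootstrap interval for it in every quadrant.

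**The case against.** A reader might infer that the plan computes a ratio whatever the signs, and that nobody could then tell a dominant programme from a dominated one. The documents do not support that reading, for three reasons.

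- The plan as a whole is not unconditional. The protocol restricts the ratio analysis in two places, the SAP says it is based on that protocol, and its summary qualifies the cost-utility analysis. Section 8 fails to repeat the restriction but does not revoke it.
- Section 8 compares QALYs and costs separately as well as forming the ratio. Dominance can be read from the signs of those two components. The sign ambiguity bites only if the ratio is reported alone, which the SAP does not say.
- The SAP promises a bootstrap, not an interval for the ratio; the interval is requested in the protocol, after the conditional sentence. Showing bootstrap pairs on a plane would fit the SAP's wording.

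It is also fair to say that the cheaper-and-better result is a conditional hope in the protocol, that the shares above rest on assumed inputs, and that net monetary benefit needs threshold values found in neither document.

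All of this stands, and it reduces the first gap to a failure to carry the condition over. It does not close the second. Neither separate comparison is said to come with an interval, the protocol's condition cannot act on individual replicates, and neither document says how the replicates are to be presented.

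**Conclusion.** The point holds in a limited form. SAP section 8 should carry the protocol's condition. Both documents leave open how to summarise replicates in different quadrants or with a QALY difference near zero, so the ratio interval requested in the protocol can be uninterpretable even where the ratio itself is allowed.

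The size depends on unknowns. If the QALY SD is 0.15 to 0.25 and the true difference is 0.02, 12% to 24% of replicates have a negative denominator at 150 per arm and 14% to 26% at 130. At a true difference of 0.05 the share is about 5% or less, and the problem largely disappears. The simulated intervals also assume normal and independent cost and QALY differences; correlation or skewed costs would change the limits, but not the reason they fail.

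This is a cheap improvement to a secondary economic objective. Neither primary analysis is touched.

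**What to change.** In SAP section 8:

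1. Report the incremental cost and the incremental QALYs separately, each with a bootstrap confidence interval.
2. Report the ratio only when both differences have the same sign, that is, when one strategy is both dearer and better. Otherwise say in words which strategy dominates. The rule should not be limited to two positive differences, because the protocol's condition also covers a control arm that is dearer and better.
3. Replace a confidence interval on the ratio by incremental net monetary benefit with its bootstrap interval over a stated range of willingness-to-pay values, plus an acceptability curve, all from the same replicates.
4. Align the bootstrap wording in protocol IX.4 with this, or record the change in the SAP.

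The cost is a few lines of text, with no new data and no extra resampling. The one real decision is the threshold range, which should be fixed before the economic results are seen.
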